### Efficacy Outcomes

A total of 9 outcome measures will be used to test preliminary evidence of training efficacy. Specifically, 7 self-assessed outcome measures (ie, 5 questionnaires for parents and 2 questionnaires for adolescents), 2 performance-based tasks assessing social cognition taken from a standardized neuropsychological battery, and a virtual reality–based assessment of everyday setting EF will be used. Questionnaires will be sent to patients and families in a sealed envelope; after completing them, participants will be required to return them to the research staff using an envelope with a postmark included in the sealed envelope within 2 weeks. The performance-based subtests assessing social cognition and the virtual reality–based assessment will be administered remotely using the Google Meet videoconference platform.

A detailed description of outcome measures is provided in Textbox 4. The sample of this study will include adolescents aged 11 to 19 years, but some measures and questionnaires have been standardized for populations having a lower maximum age range; however, they will be adopted for this study as no other measures with the same characteristics are available in the Italian language. The individual measures affected by this problem are clearly described in Textbox 4.

All outcome measures will be administered at T0 (ie, preintervention assessment), T1 (ie, immediately after the 6-month intervention), and T2 (ie, 6 months after the end of the intervention).

For the questionnaire outcomes, approaches to missing individual items will follow the guidelines for missing item procedures indicated in the manual for each questionnaire. If no guidelines for individual missing items are available, the mean of the completed items will be used to replace missing items if ≤10% are missing.

A summary of outcome measures to test training efficacy is presented in Textbox 5.

Description of outcome measures.Behavior Rating Inventory of Executive Function Second Edition (BRIEF-2)−parent form [64]: the BRIEF-2–parent form questionnaire is aimed at assessing executive functioning (EF) behaviors of children and adolescents (aged 5-18 years) in everyday life by considering their parents’ perspectives. The questionnaire is composed of 63 items referred to 9 different clinical scales (ie, inhibit, self-monitor, shift, emotional control, initiate, working memory, plan or organize, task-monitor, and organization of materials) and 3 validity scales (ie, inconsistency, negativity, and infrequency). BRIEF 2–parent form is administered to parents, who rate the frequency of executive problems of their children on a 3-point Likert scale. Raw scores on the global scale range from 63 to 189. The *t* scores (mean 50, SD 10) are used to evaluate the level of EF behaviors relative to normative samples. Higher scores indicate a worse outcome. As this questionnaire covers the age range of 5 to 18 years, scores of adolescents of 19 years have been standardized by considering norms for adolescents of 14 to 18 years.BRIEF 2–self-report form [64]: the BRIEF 2–self-report form questionnaire is aimed at assessing self-reported EF in everyday life of adolescents aged 11 to 18 years. It is composed of 55 items belonging to 7 clinical scales (ie, inhibit, self-monitor, shift, emotional control, task-monitor, working memory, and plan or organize) and 3 validity scales (ie, inconsistency, negativity, and infrequency). Raw scores on the global scale range from 55 to 165. The *t* scores (mean 50, SD 10) are used to interpret the level of EF compared to normative sample. Higher scores represent a worse outcome. As this questionnaire covers the age range 5 to 18 years, scores of adolescents of 19 years have been standardized by considering norms for adolescents of 14 to 18 years.Child Behavior Checklist 6 to 18 (CBCL 6-18) [65]: the CBCL 6 to 18 is aimed at assessing psychological adjustment and behavioral functioning of children and adolescents aged 6 to 18 years, as rated by parents. The questionnaire includes 113 items. The scores of this instrument considered for this study are total problems, internalizing problems, and externalizing problems. Raw scores of the Total Problems Scale range from 0 to 226 and are converted to *t* scores (mean 50, SD 10) to interpret the level of behavioral functioning compared to normative sample. Higher scores indicate a worse outcome. As this questionnaire covers the age range 6 to 18 years, scores of adolescents aged 19 years have been standardized by considering norms for adolescents aged 12 to 18 years.Youth Self-Report 11 to 18 (YSR 11-18) [65]: YSR 11 to 18 is aimed at assessing self-reported psychological adjustment and behavioral functioning of adolescents aged 11 to 18 years. The questionnaire includes 112 items. The scores of this instrument considered for this study are total problems, internalizing problems, and externalizing problems. Raw scores of the Total Problems Scale range from 0 to 224 and are converted to *t* scores (mean 50, SD 10) to interpret the level of behavioral functioning compared to normative sample. Higher scores represent a worse outcome. As this questionnaire covers the age range 11 to 18 years, scores of adolescents aged 19 years have been standardized by considering norms for adolescents aged 11 to 18 years.Beck Anxiety Inventory (BAI) [66]: the BAI is a 21-item questionnaire aimed at assessing state and trait anxiety in adults. In this study, the questionnaire is administered to parents to evaluate their psychological functioning. The total score is calculated as the sum of the 21 items (4-point Likert scale, ranging 0-3), with a minimum score of 0 and a maximum score of 108. Higher scores indicate a worse outcome. Specifically, a score of 0 to 21 indicates low levels of anxiety, a score of 22 to 35 indicates moderate levels of anxiety, and a score of 36 to 108 indicates potentially concerning levels of anxiety.Symptom Checklist 90 (SCL-90) [67]: the SCL-90 is a self-report questionnaire for adults aimed at measuring psychiatric symptom intensity on 9 different subscales (ie, somatization, obsessive-compulsive, interpersonal sensitivity, depression, anxiety, anger-hostility, phobic anxiety, paranoid ideation, and psychoticism). The 90 items included in the questionnaire are scored on a 5-point Likert scale (ranging 0-4), indicating the rate of occurrence of the symptoms during the last 7 days. In this study, the questionnaire is administered to parents to assess their psychological well-being. The Global Severity Index (GSI) is considered, for which the score is reported as a ratio of the sum of all items to the number of items scored. Higher scores indicate higher psychiatric symptom intensity; consistent with recommendations [65], an average score corresponding to ≥1 on the GSI enters the clinical range.Parenting Stress Index (PSI)–Short Form [68]: PSI–Short Form is a 36-item questionnaire aimed at assessing levels of stress associated with parenting in relation to different areas: parenting competence, restrictions on life introduced by parenting, parental conflict, depression, and social support. The 36 items of the questionnaire are scored on a 5-point Likert scale. The global score (PSI-total) is considered for this study, for which clinical cutoff is established at 90. Higher scores indicate higher distress.Jansari assessment of Executive Functions for Adolescents (JEF-A) [69]: JEF-A is a computerized assessment based on nonimmersive virtual reality aimed at evaluating everyday EF in adolescents aged 10 to 18 years. It is a performance-based assessment administered to adolescents. Participants are asked to plan, set up, and run a birthday party through the completion of 16 tasks resembling real-world activities. JEF-A tasks evaluate 8 constructs related to EF: planning, prioritization, selective thinking, creative thinking, adaptive thinking, action-based prospective memory, event-based prospective memory, and time-based prospective memory. All tasks are scored on a 3-point scale: 0 for failure, 1 for a partial or nonoptimal completion, and 2 for satisfactory completion. The scores for the 2 tasks for any particular construct are summed (ie, maximum of 4 possible), and this score is converted to a percentage of achievement for this construct. In addition to the 8 individual module scores, an average total percentage is computed for the whole assessment. The final raw score ranges from 0 to 32. Higher scores and percentages indicate a better EF. Although this instrument has been tested on adolescents with acquired brain injury (ABI) who are aged 10 to 18 years, in this study, we adopted it for participants aged 19 years as well to ensure comparability and a task in line with tasks related to such an age instead of administering to those adolescents the task for adults involving a multiple errand task based around a business office [70].A Developmental Neuropsychological Assessment-2 (NEPSY-2; Theory of Mind and Affect Recognition subscales) [71]: the Theory of Mind and Affect Recognition subscales of NEPSY-2 are performance-based subtests administered to adolescents and aimed at evaluating their social perception and emotion recognition skills. Theory of Mind subscale–part A measures understanding of mental functions and other people’s perspectives, and its raw scores range from 0 to 17; Theory of Mind subscale–part B examines the ability to match basic emotions (eg, happy, sad, angry, afraid, and disgusted) to specific situations, and its raw scores range from 0 to 8. The Affect Recognition subscale tests the ability to recognize emotions in facial expressions, and its raw scores range from 0 to 35. Raw scores are converted into scaled scores (mean 10, SD 3) based on age norms ranging from 1 to 19. Higher scores indicate better outcomes. As this battery covers the age range 3 to 16 years, scores of adolescents aged 17 to 19 years have been standardized by considering norms for adolescents aged 11 to 16 years.

Outcome measures to test training efficacy administered to adolescents and parents.
**Cognitive outcomes**
Jansari assessment of Executive Functions for Adolescents (JEF-A; performed by the adolescent) [69]A Developmental Neuropsychological Assessment-2 (NEPSY-2; performed by the adolescent) [71]Behavior Rating Inventory of Executive function 2 (BRIEF 2-self-report form; related to self-functioning. filled by the adolescent) [64]Behavior Rating Inventory of Executive function 2 (BRIEF 2-parent form; related to the adolescent, filled by the parent) [64]
**Behavioral or psychological outcomes**
Youth Self-Report 11 to 18 (YSR 11-18; related to self-functioning, filled by the adolescent) [65]Beck Anxiety Inventory (BAI; related to self-functioning; filled by the parent) [66]Child Behavior Checklists 6 to 18 (CBCL 6-18; related to the adolescent, filled by the parent) [65]Parenting Stress Index (PSI; related to self-functioning, filled by the parent) [68]Symptom Checklist-90 (SCL-90; related to self-functioning, filled by the parent) [67]

### Sample Size and Power Calculation

A previous meta-analysis on the effects of the original American TOPS program on the various outcomes found a small-to-medium average effect size (Hedges *g*=0.37) [37]; however, high variability was found among the effect sizes of the different studies analyzed. This led us, to be conservative, to estimate a small effect size of f=0.2 for the evaluation of the power calculation in the present study. Power analysis was conducted using G*Power3 Software (Heinrich-Heine-Universität Düsseldorf) [72,73]. Assuming a correlation of 0.50 between repeated measures and setting the α level at *P*<.05, a sample size of 21 participants per group will be required to obtain 80% of power with our 2 group- and 3 time-point- design. Therefore, a whole sample of 42 participants will be required to be included in the study. Attrition was not considered in performing power calculation, as adherence rates will be a core outcome of this study, which is pioneering for the Italian context and, therefore, will be aimed at collecting data on feasibility. Therefore, any eventual dropouts will be accounted for in statistical analyses using intention-to-treat analysis procedures.

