**Results:**

This study started on February 26, 2021, and ended on February 28, 2023. A total of 42 adolescents were enrolled and randomly assigned to the 2 study groups, 34 (81%) completed the intervention and posttreatment evaluation (I-TOPS: n=19 and wellness intervention: n=15) and 31 performed follow-up evaluation (I-TOPS: n=18 and wellness intervention: n=13). Data analysis on feasibility and efficacy will be performed after protocol publication, and the results will be published in the form of a paper in a relevant journal in 2025.

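### The planning effect f=0.2 is called conservative but is larger than the cited g=0.37, so the stated 80% power does not apply to the effect the protocol cites

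*Protocol article*

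**What the plan says.** The section Sample Size and Power Calculation starts from a meta-analysis of the original programme, which "found a small-to-medium average effect size (Hedges *g*=0.37"), and notes that the effects varied widely between studies. It continues: "This led us, to be conservative, to estimate a small effect size of f=0.2". The remaining inputs are given as "Assuming a correlation of 0.50 between repeated measures and setting the α level at *P*<.05". The result is that "a sample size of 21 participants per group will be required to obtain 80% of power with our 2 group- and 3 time-point- design", so 42 in total. The software is G*Power 3; the effect tested (group, time or their interaction) is not named.

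On dropout, the same section says: "Attrition was not considered in performing power calculation, as adherence rates will be a core outcome of this study". It adds that dropouts will be dealt with through intention-to-treat procedures. The Data Analysis Plan specifies linear mixed models with time, treatment and their interaction, on available data without imputation. Post hoc tests follow a significant interaction or group effect.

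The abstract reports 34 participants at the post-treatment assessment (19 and 15), and "31 performed follow-up evaluation (I-TOPS: n=18 and wellness intervention: n=13").

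**The concern.** Hedges g is a difference between groups in SD units. Cohen's f is the SD of the effects divided by the within-group SD. Placing 0.2 next to 0.37 makes 0.2 look like a cautious reduction, but once both are on one scale it is an increase. The reason given for the choice, high variability between studies, calls for a smaller planning effect, and the number chosen goes the other way.

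Two things are at stake. First, readers will take the trial to have 80% power against something smaller than the effect cited, when it has less than 80% against that effect itself. Second, the article treats intention-to-treat analysis as the answer to dropout in the power calculation. Analysing everyone as randomised guards against bias, but it does not recover the information in assessments that were never made.

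**Working it through.** **Inputs.** From Sample Size and Power Calculation: g=0.37, f=0.2, correlation ρ=0.50, α=0.05, k=2 groups, m=3 time points, N=42. From the abstract: 34 observed at T1 (19/15) and 31 at T2 (18/13).

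**1. Reproduce the plan's figure.** For G*Power's within-between interaction with its default effect size, λ = f²·N·m/(1−ρ), df1 = (k−1)(m−1) = 2, and df2 = (N−k)(m−1) = 80.

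- N=42: λ = 0.04 × 42 × 3/0.5 = 10.08, power 80.3%.
- N=40: λ = 9.60, power 78.2%.

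So 42 is the smallest even N that reaches 80%, as stated. The group main effect at f=0.2 gives only 34% at N=42 (134 needed), and G*Power's SPSS-type effect-size option gives 33%. A pure time effect has the same λ and df as the interaction, but it does not compare the treatments. The interaction is therefore the natural reading, though it is inferred.

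**2. Simple conversion.** f = g/2 = 0.37/2 = 0.185, which is below 0.2. In reverse, f=0.2 is d=0.40, which is above 0.37. This step needs no assumption about time pattern or correlation. Entering f=0.185 directly as the interaction f gives λ = 0.034225 × 42 × 6 = 8.62 and power 73.5%; N=50 would be needed for 80%.

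**3. Conversion on the interaction scale.** Assume no difference at T0 and a difference d at both T1 and T2. The mean difference over time is 2d/3. Splitting the deviations from it equally between the groups gives ±(−d/3, d/6, d/6). The mean square is (d²/9 + d²/36 + d²/36)/3 = d²/18, so f = d/√18.

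- g=0.37: f = 0.37/4.243 = 0.087, λ = 1.92, power 21% at N=42; about 214 participants would be needed for 80%.
- f=0.2: d = 0.2 × 4.243 = 0.85 SD, and 0.85/0.37 ≈ 2.3 times the cited effect.

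If the effect builds gradually (0, d/2, d), then f = d/√24. Now f=0.2 means 0.98 SD at T2, and power for g=0.37 is 17%.

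**4. Sensitivity to correlation** (g=0.37 at T1 and T2, N=42):

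| ρ | Power |
|---|---|
| 0.3 | 16% |
| 0.5 | 21% |
| 0.7 | 33% |
| 0.8 | 47% |

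The gradual pattern is lower at each ρ (for example 13% at 0.3 and 37% at 0.8).

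**5. Attrition.** The planned mixed model uses every available observation, so the retained participants should not be treated as a complete-case sample. Generalised least squares with 42, 34 and 31 observed at T0, T1 and T2 (equal difference at T1 and T2, ρ=0.5, about 61 denominator df) gives:

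- at the plan's f=0.2: λ = 8.42, power about 72%;
- for g=0.37: λ = 1.60, power about 18%.

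**The case against.** The arithmetic is internally correct: the stated inputs do return 42. The fault is in the choice and labelling of the effect size, and a reader should not infer a computational error.

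A reader might also conclude that the trial simply has 21% power. The document does not support that as a fact. It gives no time pattern for the effect, does not say how g was standardised or pooled across outcomes, and does not name the test. The 21% rests on assumptions about all three, and under the most favourable conversion the figure is 73.5%. What is firm is the direction: f=0.2 exceeds the cited effect on either conversion, and 80% is not reached for it at the plan's own correlation. A higher correlation would help. With f=0.185 entered directly, power passes 80% at ρ=0.6 (83%), but the plan assumes 0.50.

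On attrition, the omission is openly disclosed with a feasibility reason, so nothing is concealed. Treating the 34 or 31 retained as the whole sample would give 70.5% or 66.0% at f=0.2, and 66% is too pessimistic for a mixed model that also uses the earlier assessments of those who left. What stands is that intention-to-treat handling does not make up the loss.

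Finally, one might predict that a null result will be read as inefficacy. The article does not say so: it describes the efficacy evidence as preliminary and makes a phase 3 trial conditional on positive results. The case for correction rests on the power statement, not on that prediction.

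**Conclusion.** The point holds. The label is wrong without further assumptions: f=0.185 for g=0.37 against the 0.2 used. If the test is the interaction, with equal baselines, the same difference at T1 and T2, ρ=0.5, sphericity, and g in between-group outcome-SD units, the design has 80% power for about 0.85 SD and about 21% for 0.37 SD. For ρ from 0.3 to 0.8 the latter runs from about 16% to 47%. At the plan's ρ, 73.5% is the ceiling under the simple conversion. The reported attrition lowers these further, to about 72% at f=0.2 and about 18% for g=0.37 at ρ=0.5.

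The follow-up count is itself uncertain: the main Results section says 34 had both the post-training and 6-month evaluations, whereas the abstract gives 31 at follow-up. The attrition figures here use the abstract. Using 34 at T2 would raise them somewhat but not to the full-sample values.

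**What to change.** No further enrolment is called for. In Sample Size and Power Calculation:

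- delete the claim that f=0.2 is conservative;
- name the effect that was powered;
- state the difference detectable with 80% power (about 0.85 SD at T1 and T2 if the test is the interaction), with its assumptions;
- give power for g=0.37 as a range: about 16% to 47% on the interaction scale for correlations of 0.3 to 0.8, at most about 74% under f=g/2 at the plan's correlation, and lower with the observed attrition;
- say that intention-to-treat handling does not restore the power lost to dropout.

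In the Data Analysis Plan, state that efficacy will be read from estimates with 95% confidence intervals and that non-significance is not evidence of no effect.

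The correction should not say that 42 was set by feasibility. The Introduction and the sample size section both attribute it to the power analysis, and feasibility is offered only as the reason for leaving out attrition.

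The cost is wording, plus a less favourable power statement. The article says analysis will follow its publication, so the correction should be in place before results are reported.

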### Data Analysis Plan

All randomized adolescents will be included in the analyses, irrespective of adherence to treatment in the I-TOPS or wellness intervention. No imputation of a missing baseline or follow-up data will be performed. The *t* tests and chi-square analyses will be performed to compare the I-TOPS (ie, experimental) and wellness (ie, control) intervention groups on continuous and dichotomous variables, respectively. Similar analyses will be performed to examine baseline differences between patients who will complete the study and those who will drop out. Frequencies and means related to feasibility outcomes will be calculated. Analyses will be performed using SPSS (version 29.0.1.0; IBM Corp) [74].

Efficacy outcome measures will be separately entered into linear mixed effect models with “time” (baseline vs immediately after treatment vs 6-month follow-up) and “treatment” (regular I-TOPS vs wellness intervention) and their interaction as fixed factors and “intercepts” and “participants” as random factors. In case of differences in any clinical or demographic variables between groups at baseline, those measures will be included in the analyses as covariates. Mixed model analysis allows flexible modeling of the pattern of change over time and uses all the data for a given participant, even if that participant is not seen at all assessments, allowing us to retain participants with missing assessments. Significant interaction effects (ie, time and group) or group effects will be analyzed by post hoc tests. The significance threshold will be set at <.05. No interim analysis will be planned.

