### Data Collection

Following completion of the consent process, sociodemographic information (eg, age, sex, and socioeconomic status); details of past medical history; concurrent medication; the adolescent’s age at the time of injury; and injury severity, measured using the Glasgow Coma Scale [61] will be collected from each patient’s referring physician. Family compositions will be collected from parents via telephone for outpatients or directly in the clinic for hospitalized patients who are close to discharge.

At baseline (T0), after treatment (T1), and at 6-month follow-up (T2), adolescents and parents will be asked to complete study outcome measures, including questionnaires on cognitive and behavioral functioning of adolescents, and the psychological well-being of parents and adolescents will undergo remote cognitive performance–based evaluations. Questionnaires will be sent to adolescents and families in a sealed envelope; after completing them, adolescents and parents will be required to return them to the research staff using an envelope with a postmark included in the sealed envelope within 2 weeks. To promote participant retention, support from a member of the research team could be given for questionnaire fulfillment, if needed. In addition, performance-based measures on adolescents’ cognitive functioning will be remotely administered, thus removing practical barriers to patient retention in the study, such as difficulties in transportation and reaching research centers.

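### If a baseline covariate chosen for adjustment has missing values, the no-imputation rule would keep some randomised adolescents out of the adjusted models

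*Protocol article*

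**What the plan says.** Three rules stand together in the protocol article, under Data Analysis Plan.

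- Population: "All randomized adolescents will be included in the analyses, irrespective of adherence to treatment in the I-TOPS or wellness intervention".
- Missing data: "No imputation of a missing baseline or follow-up data will be performed".
- Covariates: "In case of differences in any clinical or demographic variables between groups at baseline, those measures will be included in the analyses as covariates".

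The model has treatment, time and their interaction as fixed factors. The levels of time are "baseline vs immediately after treatment vs 6-month follow-up", so the baseline value of each outcome is part of the repeated response and is not a covariate. The article justifies the mixed model by saying that it uses a participant's data "even if that participant is not seen at all assessments, allowing us to retain participants with missing assessments".

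Under Data Collection, sociodemographic data, past history, medication, age at injury and injury severity (Glasgow Coma Scale) "will be collected from each patient’s referring physician". Family composition comes from the parents. Under Randomization and Blinding, allocation follows consent and the baseline measures, and there is no stratification. The only replacement rule in the article, under Efficacy Outcomes, is for single questionnaire items.

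**The concern.** A likelihood-based mixed model copes with a missing outcome visit: the participant's other visits stay in. It does not cope with a missing value in a covariate that is constant over time. Such a value is missing on every row of that adolescent, so every row is dropped. The retention property that the article relies on therefore does not extend to the adjusted models it also plans.

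The usual remedy is to fill in the covariate without looking at arm or outcome. On its natural reading, the ban on imputing baseline data rules this out.

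At stake is whether the adjusted analysis is the all-randomised one. Adolescents with complete outcomes could leave it for a reason unrelated to follow-up, and possibly unevenly by arm. The trial has 42 participants, and its sample size makes no allowance for attrition.

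**Working it through.** **1. The plan's own sample size.** Inputs from Sample Size and Power Calculation: f = 0.2, correlation 0.50, alpha 0.05, 2 groups, 3 time points, 21 per group. For the group-by-time interaction in a repeated-measures ANOVA:

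- noncentrality = f² × N × m / (1 − ρ) = 0.04 × 42 × 3 / 0.5 = 10.08
- df1 = (2 − 1)(3 − 1) = 2; df2 = (42 − 2)(3 − 1) = 80
- power from the noncentral F = 0.803

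The smallest even N that reaches 80% is 42, so the stated figure reproduces.

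**2. What the model drops.** A random-intercept model was fitted to simulated data for 42 adolescents, using complete rows only. Retention followed the Abstract: 42 at baseline, 34 after treatment and 31 at follow-up, so 42 + 34 + 31 = 107 records. (The Results section instead says that 34 had both later evaluations. This does not affect the mechanism.)

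| Situation | Records | Adolescents |
|---|---|---|
| No covariate, or a complete covariate | 107 | 42 |
| Baseline outcome missing for 2 | 105 | 42 |
| Covariate missing for 2 completers, adjusted model | 101 | 40 |
| Same data, unadjusted model | 107 | 42 |

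The fall from 107 to 101 is 2 adolescents × 3 visits. A missing baseline outcome costs one record and no adolescent. A missing covariate costs the whole adolescent.

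**3. Can it happen?** Two things must coincide: a variable is selected because the groups differ on it, and that same variable has a gap.

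- Selection: Data Collection names about eight candidates (age, sex, socioeconomic status, past history, medication, age at injury, injury severity, family composition). If each were tested independently at 5%, which is an assumption because the article gives no threshold, the chance of selecting at least one is 1 − 0.95⁸ = 0.34.
- A gap: the documents give no missing rate. For one variable with an assumed rate q, the chance of at least one missing value among 42 is 1 − (1 − q)⁴².

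| Assumed q | Chance of at least one gap |
|---|---|
| 1% | 0.34 |
| 2% | 0.57 |
| 5% | 0.88 |
| 10% | 0.99 |

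The most plausible candidate is the Glasgow Coma Scale. Eligibility Criteria admit stroke, infection or inflammation and anoxia as well as trauma, at least one year after the event. A coma score may not have been recorded in some of these cases.

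**4. Size, for an assumed k of 42 lost.** Standard error ratio = √(42 / (42 − k)). Power uses the formula in step 1 with N = 42 − k.

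| k | N | SE ratio | Noncentrality | df2 | Planning power |
|---|---|---|---|---|---|
| 0 | 42 | 1.000 | 10.08 | 80 | 0.803 |
| 2 | 40 | 1.025 | 9.60 | 76 | 0.782 |
| 4 | 38 | 1.051 | 9.12 | 72 | 0.758 |

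These are planning-scale figures. They assume that the lost adolescents carry average information, and they ignore both dropout and any precision gained from the covariate.

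**The case against.** **The rule may mean assessments only.** The article uses baseline and follow-up as levels of time and then speaks of missed assessments. On that reading the ban already concerns outcomes, and the article is merely silent on covariates, which a condensed article may leave to the full plan. The reading is possible, but it is not the natural one: the sentence covers missing baseline data without qualification. A fuller plan that filled in covariates would appear to contradict it.

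**The all-randomised sentence is about adherence.** This is partly right, since it is worded with adherence in mind. It still states that everyone randomised is analysed, and Sample Size and Power Calculation also relies on intention-to-treat procedures.

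**Missing values are unlikely.** Candidates are found by reviewing medical records at one institute together with the referring physicians, and baseline measures precede randomisation. This makes wide loss less likely. It does not guarantee each clinical history item, because Data Collection describes these apart from the outcome measures taken at baseline.

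**Filling in weakens adjustment.** This stands. A covariate enters because the arms were seen to differ on it, and an overall mean adjusts less for that difference. Where a coma score does not apply, a mean has no clear meaning.

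**Stronger readings that the documents do not support.** A reader might infer that:

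- the all-randomised analysis is certain to fail, but covariates enter only after a baseline difference and no missing covariate is reported;
- a missing baseline outcome also removes an adolescent, which step 2 shows is not so;
- different adolescents would be lost from outcome to outcome, but covariates are chosen once from clinical and demographic variables, so a gap removes the same adolescents from every adjusted model;
- a large share of the sample could go, for which nothing in the documents gives a basis.

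**Conclusion.** The point holds in conditional form. If a variable selected for adjustment has missing values, the adjusted models would not include all randomised adolescents, and the mixed model's handling of missed visits does not prevent this. As worded, the plan also bars the standard remedy, so this is a rule that works against the plan's own aim and not only an unstated detail.

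The effect is modest: for 2 or 4 adolescents lost, a standard error about 2.5% or 5% larger and planning power of about 0.78 or 0.76 in place of 0.80. Both counts are assumptions. The more important cost is that participants with complete outcomes could leave an analysis described as intention-to-treat. If all selected covariates prove complete, or none is selected, nothing is lost.

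**What to change.** In the Data Analysis Plan:

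1. Limit the no-imputation rule to outcome data.
2. Add a rule such as: a missing baseline covariate is replaced by the mean of that variable over all randomised adolescents, or by a not-recorded category if it is categorical, without use of arm or outcome. Where the measure does not apply to a type of injury, an indicator is added. Every randomised adolescent with any outcome record then stays in every model.
3. Report the unadjusted model on all randomised adolescents next to the adjusted one, with the number of adolescents and of filled-in values for each.

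The covariates precede randomisation and the replacement is blind to arm and outcome, so it does not by itself favour either group. The downside is slightly weaker adjustment for the observed imbalance among those with filled-in values; the unadjusted model gives a comparison that does not depend on the replacement.

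The cost is a few lines of text and data preparation, with no new data. The Abstract and Results both place the analysis after publication of the protocol, so the rule can be set before results are seen.
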